#### Secondary Outcome Measures

Blood pressure (BP) (pre- and post-6MWT),Heart rate (HR) (pre- and post-6MWT),Blood oxygen saturation,Spirometry FVC, FEV1, FEF 25–75,Compass 31 (Autonomic function self-report),Zung Depression Inventory,Zung Anxiety Inventory,COPD Assessment Test (CATest),FA Health Questionnaire,Multidimensional Assessment of Interoceptive Awareness (MAIA),Borg Dyspnea Scale,Heart Rate Variability (HRV),2 Ewing tests,Urine analysis (melatonin and cortisol),Saliva analysis (diurnal cortisol), andBlood (fingerprick) analysis.

All tests are administered by trained researchers. Blood, urine, and saliva analysis provided by ZRT Laboratory, Beaverton, OR, USA.

### Outcome Measurement Details

#### General Health

##### Flight Attendant Health Questionnaire

This was developed by [name] at the Harvard School of Public Health. Its use provides us with a health and FA-related occupational history and enables us to compare our study results with those of [name].

#### Functional Ability

Exercise endurance and tolerance is evaluated by the 6MWT followed by the Borg Dyspnea inventory. This is used as our principal outcome measure since it is a well-recognized measure of overall functional ability. The walk is conducted on an indoor level surface free of obstructions. Research assistants are on hand to assist participants with any difficulties. Maximum distance walked in 6 min is recorded (53–55). The difference in scoring from baseline to the end of study is calculated for each participant. *The Borg Dyspnea Inventory*, a well-established instrument for measuring respiratory distress, is administered following the 6MWT. The 6MWT is subject to variation due to motivation; the addition of the Borg instrument increases the reliability of the test.

#### Respiratory Health

##### The COPD Assessment Test

The CATest is used as an initial recruitment screening as well as an outcome measure. Volunteers must score above 5 for inclusion in the study. Its main purpose is to eliminate those with no appreciable respiratory dysfunction.

#### Spirometry

##### FEV1/FVC and Flow/Volume Curves

Forced expiratory volume in 1 s to forced vital capacity and Flow/Volume Curves are used as part of the inclusion criteria (see above under inclusion criteria), and to determine the degree of pulmonary dysfunction. We use specific validated spirometric cut points (56). We record FEV1/FVC ratio and Flow/Volume Curves using the EasyOne Plus Frontline spirometry system. FEV1/FVC is a standard measurement used to determine the GOLD grade of COPD. The Flow/Volume Curves indicate the degree of pulmonary dysfunction; participants with no detectable pulmonary dysfunction are excluded from the study. The differences in scoring from baseline to specific intervals are calculated for each participant.

#### Cardiovascular Measures

##### Blood Pressure and Heart Rate

Blood pressure and HR are measured at the beginning of each testing period and before and after the 6MWT by a trained technician using standard clinical instruments. *Cardiac R-R intervals* are recorded over the entire testing period (about 1½ h) using a commercially available system, the Holter myPatch 24-h single channel AMS3000 from DMS-Services, Los Angeles, CA, USA. This is a non-intrusive device, using two electrodes. Due to problems with availability, this measure was not included with some participants during the Selection stage of the study only. Blood oxygen saturation is also measured, using a Choicemmed Oxywatch Fingertip Pulse Oximeter.

#### Autonomic Condition

##### Heart rate Variability

Subjects are asked to sit quietly for 10 min. In post-analysis, the HR data collected during these periods is used to calculate HRV. HRV data will be analyzed using software provided by the manufacturer: CardioScan II, version 12.4.0054a, from DMS Software, Los Angeles, CA, USA. Time domain (SDNN, RMSSD) and frequency domain [power spectral density (PSD)] analysis methods will be used. [name], Director of the Washington University School of Medicine HRV Lab, will serve as a consultant on HRV analysis and interpretation. HRV measurements are only available for a subset of participants in the Selection stage due to delayed availability of HR monitors; monitors will be fully available during the RCT stage.

##### Ewing Tests

The Ewing tests evaluate cardiac autonomic function by measuring the response of HR or blood pressure to a physical challenge. We will administer two of the battery of five Ewing Tests: deep breathing heart rate challenge (DBHR) and lying to standing blood pressure challenge (LSBP). DBHR has been determined to be the most significant of the Ewing tests, carrying 80% of the significance. To measure this, participants will be asked to breathe deeply for three 1-min periods at a rate of six times a minute; post-analysis using recorded R-R intervals will enable evaluation of HR response to challenge, which is a measure of the integrity of the sympathetic branch of cardiac autonomic control. To measure LSBP, the systolic blood pressure change from supine to standing is measured. This gives an indication of cardiac parasympathetic function. Comparing the results from HR, BP, HRV, DBHR, and LSBP will allow a more accurate evaluation of the cardio-respiratory autonomic system than any one of them taken alone. Full Ewing test results are only available for a subset of participants due to problems with availability of the heart monitors.

##### COMPASS 31

In addition, we administer the COMPASS 31, a questionnaire for detecting dysfunction in many aspects of the ANS.

#### Affective State

##### Zung Anxiety and Depression Inventories

These evaluate the degree of affective disturbance. They are both well validated and widely used instruments. Since depression and anxiety are significant co-morbidities of COPD, and since we speculate that MM intervention will have an impact on them, the Zung inventories are relevant.

#### Interoceptive Awareness

##### The Multidimensional Assessment of Interoceptive Awareness (MAIA)

The Multidimensional Assessment of Interoceptive Awareness (MAIA) is a questionnaire that evaluates the degree of a person’s awareness of interoceptive cues, as well as his or her degree of comfort with these cues. We believe this is relevant to a person’s ability to benefit from the MM intervention.

#### Biomarkers

Biomarkers include urine, saliva, and blood analysis.

##### Blood Analysis

Capillary blood drops will be taken from the finger following fingerprick with a lancet, and deposited onto a blood spot card used specifically for dried blood spot (DBS) collections. Blood spots are dried on the filter card for at least 2 h before closing the cover and then further dried overnight at room temperature before storing the cards for shipment to ZRT Laboratory. Six-millimeter disks of blood spots are punched into 96-well plates and the blood extracted with buffers. Extracts are assayed for C-reactive protein (CRP), a marker of inflammation, as well as HbA1c (a marker of metabolic function), thyroid stimulating hormone, and Vitamin D.

##### Urine Steroid Hormone and Element Testing

Participants will be asked to provide first morning and then a bedtime urine samples: these are collected onto an absorbent paper strip and dried. They will be instructed in correct procedures for this. The sample will later be analyzed at ZRT Lab to determine by LC-MS/MS levels of urinary free cortisol, free cortisone, and melatonin, and by ICP-MS levels of iodine, bromine, selenium, arsenic, cadmium, and mercury (all normalized to creatinine).

##### Salivary Steroid Hormone Testing

Participants are instructed to provide four saliva samples over the course of a day. These samples will be stored frozen and batch-shipped to ZRT Laboratory and analyzed to determine diurnal cortisol levels as well as first morning estradiol, progesterone, testosterone, and dehydroepiandrosterone (DHEA) by LC-MS/MS.

Dried blood spots, dried urine (DU), and saliva samples are mailed to the researchers and stored at −70°C until they can be shipped in bulk to ZRT Labs for testing.

This extensive range of biomarkers will allow us to examine correlations between levels of function of a wide range of physiological systems and pulmonary dysfunction.

During the Selection and RCT stages of the study, feedback will be gathered from participants through written logs, and a questionnaire on Survey Monkey. Copies of the forms for the written logs and the Survey Monkey questionnaire are available as Supplementary Material.

### Statistical Methods

Descriptive statistics, including mean, SD, and frequency, will be used to describe and summarize baseline data. We will also compare distributions between intervention and control groups in the RCT stage using Wilcoxon rank-sum tests and chi-square tests at baseline. An intent-to-treat analysis will be carried out where missing data will be handled by multiple imputation approach, and linear regression models will be used to compare the intervention group with the control group in terms of the primary outcomes.

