#### Randomization and Blinding

The Screening and Selection stages of this study do not use a control group; blinding and randomization are, therefore, not necessary. In the RCT, participants will be stratified by gender, age, and severity of pulmonary dysfunction and randomized to an intervention groups and an attention control, using the covariate adaptive randomization method (51). This method accommodates recruitment and testing over an extended period of time. Full blinding of participants to intervention is not possible under these circumstances; however, all scoring of tests will be done by assistants blinded as to participant group.

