#### Sample Size

The Screening stage of this study has no limit on number of participants. For the Selection and RCT stages of the study, we determined that, based on a predicted difference of 46 m in the 6-min walk test (6MWT) and an assessment of previous similar studies of MM for COPD, this study required a sample size of 20 participants in each group to achieve a statistical power of 80% at a significance level of 5%. To compensate for anticipated dropout, we recruited a total of 27 participants into the Selection group. On the basis of our experience of a high dropout and non-compliance rate in the Selection stage (~40%), we intend to recruit 120 participants for the RCT, 60 for each group.

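### The primary regression states no baseline term, allocation factor or hs-CRP scale; run as written, on change by arm, it is valid but gives up precision that costs nothing to recover

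*Protocol article*

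**What the plan says.** Four statements in the protocol article bear on this point.

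- **Outcomes.** Primary Outcome Measures lists the 6-minute walk test (6MWT) and, explicitly as a change, hs-CRP. Functional Ability adds for the 6MWT: "The difference in scoring from baseline to the end of study is calculated for each participant".
- **Allocation.** Under Randomization and Blinding, "participants will be stratified by gender, age, and severity of pulmonary dysfunction", with assignment by a covariate-adaptive method.
- **Primary analysis.** Statistical Methods specifies intent to treat with multiple imputation, and says that "linear regression models will be used to compare the intervention group with the control group in terms of the primary outcomes". It names no covariate and no scale.
- **Baseline data.** The only between-arm use stated is to "compare distributions between intervention and control groups in the RCT stage using Wilcoxon rank-sum tests and chi-square tests at baseline".

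No section connects the three allocation factors, or the baseline values of the outcomes, to the regression model.

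**The concern.** A reader who carries out Statistical Methods exactly as worded would regress change on arm and stop there. Three things would then be lost.

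1. Subtracting baseline uses it with a fixed coefficient of 1. Fitting it as a covariate lets the data choose the coefficient and is never less precise in large samples.
2. The allocation forces balance on gender, age and severity. That makes the true sampling variance of the treatment effect smaller. A model without those factors leaves their contribution in the residual, so its standard error is too large.
3. hs-CRP is a concentration that may be strongly right-skewed. An arithmetic change would then be dominated by a few high values.

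All three cost power. hs-CRP is the more exposed outcome, because Sample Size rests on the 6MWT alone and gives no power for hs-CRP.

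**Working it through.** **The plan's own figure.** Sample Size gives 20 per group for 46 m, 80% power and 5% significance, but no SD; it refers only to "an assessment of previous similar studies of MM for COPD". The figure can therefore be solved backwards but not reproduced. For a two-sided test by the normal approximation:

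SD = 46 / [(1.960 + 0.842) × √(2/20)] = 46 / 0.886 = 51.9 m.

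With an SD of 40, 60 or 80 m, the requirement would be 12, 27 or 48 per group. Below, 51.9 m is taken as the SD of change.

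**Step 1: baseline adjustment.** With equal variance σ² at both visits and correlation r, the change score has variance 2σ²(1−r). The baseline-adjusted outcome has σ²(1−r²). The ratio is

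(1−r²) / [2(1−r)] = (1+r)/2.

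The documents give no r, so a range is shown:

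| Assumed r | Variance ratio | Reduction | n per group in place of 20 | Power at n = 20 |
|---|---|---|---|---|
| 0.5 | 0.75 | 25% | 15 | 90% |
| 0.7 | 0.85 | 15% | 17 | 86% |
| 0.8 | 0.90 | 10% | 18 | 84% |
| 0.9 | 0.95 | 5% | 19 | 82% |

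**Step 2: allocation factors left out.** Suppose the factors explain a share R² of the variance of the analysed outcome and are perfectly balanced. The model standard error is then too large by 1/√(1−R²), and the true two-sided size of a nominal 5% test is 2 × [1 − Φ(1.96/√(1−R²))]. The last two columns simulate minimisation with 72 participants (60 per arm, 40% lost), 4,000 runs:

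| Assumed R² | Size by formula | Simulated, factors omitted | Simulated, factors included |
|---|---|---|---|
| 0.05 | 4.4% | 4.7% | 5.4% |
| 0.20 | 2.8% | 3.7% | 5.2% |
| 0.30 | 1.9% | 2.1% | 4.9% |

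Real minimisation balances imperfectly, so the simulated loss is smaller than the formula gives. Apart from simulation error, including the factors restores the nominal level.

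**Step 3: scale of hs-CRP.** The assumptions are a lognormal outcome, log-scale SD 0.8, r = 0.6, a true ratio of 0.65 (a 35% reduction) and 36 per arm. Simulated power, good to about 2 percentage points:

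- raw change: 42%
- raw follow-up adjusted for raw baseline: 63%
- log change: 70%
- log follow-up adjusted for log baseline: 79%

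With log SD 1.0, the first and last become 26% and 61%. How the gain of 79 − 42 = 37 points divides depends on the order of the steps. Adjusting first gives 21 points for baseline and 16 for the log. Taking logs first gives 28 for the log and 9 for baseline.

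**Step 4: does the 6MWT target survive without adjustment?** Pitfalls, Artifacts, and Troubleshooting allows for up to 60% dropout, leaving 60 × 0.4 = 24 per arm. At the roughly 40% seen in the Selection stage, 60 × 0.6 = 36 remain. With SD 51.9 m, power is 87% and 96%. The loss would not take the 6MWT below 80% if that SD is right.

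**The case against.** The strongest reply is that the article never says the model is unadjusted. Linear regression accommodates baseline, gender, age, severity and a log response, and covariate lists and transformations are commonly left to a full protocol or SAP, which is not shown. That reply stands. A reader might infer that the plan fixes an unadjusted analysis with hs-CRP on its raw scale, but the documents do not support this: they exclude no covariate, and a change in hs-CRP could be a log change.

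Nor is a change score itself the defect. Change regressed on arm and baseline gives the same treatment estimate and standard error as follow-up regressed on arm and baseline. Only a missing baseline term costs precision.

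A reader might also infer that mismatched standard errors make the trial prone to false positives. The direction is the opposite: the test is conservative.

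Finally, every magnitude rests on assumed r, R², log SD and effect. R² may be low for a change score, since subtraction already removes much stable variation due to age, gender and severity; at 0.05 the size effect is negligible. The skewness of hs-CRP is likewise not in the documents.

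What remains is that the article commits to change as the outcome and to covariate-adaptive allocation, and joins neither to the model it names. Followed as worded, it yields the less precise analysis.

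**Conclusion.** The point holds as a free gain in precision, not as the correction of an invalid analysis. Taken literally, the stated comparison has a variance that baseline adjustment would reduce by 10% to 25% (r of 0.8 to 0.5), and its nominal 5% test has a true size of about 4.4% to 1.9% (R² of 0.05 to 0.3, perfect balance). For the 6MWT this is modest and does not threaten 80% power if the SD is near the implied 51.9 m. The larger practical risk is hs-CRP: if it is right-skewed and analysed as a raw change, power could be about half of what a log-scale adjusted analysis gives (42% against 79% in the assumed case).

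The baseline significance tests are a minor side point. Between properly randomised arms any difference is due to chance, so the tests answer no useful question, but dropping them changes no primary result.

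**What to change.** State in Statistical Methods, or confirm in the SAP:

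- **6MWT:** week-52 distance regressed on arm, baseline distance, gender, age and the severity factor as used in the allocation.
- **hs-CRP:** log week-52 value regressed on arm, log baseline value and the same three factors, reported as a ratio of geometric means with its confidence interval.
- **Imputation:** the same variables, on the same scales, in the multiple imputation model.
- **Baseline table:** optionally, descriptive summaries by arm in place of the Wilcoxon and chi-square tests.

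The cost is wording only. The plan already collects every variable, and sample size, visits and procedures do not change. The choice should be fixed before anyone sees outcome data by arm.

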### Stepwise Methods

Stepwise methods are detailed in Figure 4.

**Figure 4 F4:**
[figure not shown]
**Proposed timeline for the study**.

### Anticipated Results

In the Selection and the RCT stages of this research, it is anticipated that subjects in the study will increase endurance as demonstrated by an increase in the 6MWT by margins that meet or exceed statistical significance. A general marker of inflammation, hs-CRP, is expected to decrease significantly. Consistent with evidence that MM may benefit the ANS, we expect to see a decrease in blood pressure. With the larger number of subjects in the RCT stage of the study, secondary measures are expected to provide data suggesting or discounting relationships between ANS function, mood, pulmonary, and immune system functions.

### Pitfalls, Artifacts, and Troubleshooting

A potential pitfall in this study is the difficulty in recruiting and retaining subjects. Our extensive network of contacts among FA will facilitate this process, as will our outreach through FA-connected social media. The recruitment process can be extended in time to assure adequate numbers. In addition, the researchers are prepared to travel to locations throughout the country as necessary.

Retention of subjects in the second and third stages is another concern. It is anticipated that retention will not exceed the 40% of the Selection stage of the study, as the exercises to be taught are simple and enjoyable. However we are allowing for up to 60% drop-out rate. Should dropout be more than anticipated, we will need to recruit more subjects, which should prove possible. We have maintained good communication with all subjects.

In the Selection stage of the study, any difficulties participants have had with the training, including safety-related concerns, were explored as a source of information concerning appropriate selection of exercises; this was one of the aims of this portion of the study.

The smoking status of study participants is queried during the recruitment and further during testing for each stage of this study. However, additional details of a smoking history have, in a few cases, emerged when other data had already been collected on these subjects. Outcomes from these subjects will be sequestered and reported separately from those who smoked less than 100 cigarettes in a lifetime.

Due to limited availability of equipment, the wearable ECGs were not used in the majority of pre-testing in the Selection stage. Changes in HRV are, therefore, not documented. However, other measures of cardiovascular autonomic function were made, including HR, BP, and changes in these measures in response to challenge. These will provide some information about possible autonomic changes.

In the Selection stage, we do not use a control group. Since the purpose of this portion is to determine that MM exercises are most effective and best tolerated, use of a control group would not be appropriate. This diminishes the power of results from the pre-and post-intervention tests in this portion as it will not be possible to determine with certainty whether results are due to attention, seasonal or other factors. However, the final RCT stage of the study, using an attention/health education control group, will provide a well-controlled validation of the effects of the selected MM exercises. It is, however, possible that positive results from the testing in the Selection stage, followed by negative results from the RCT stage, would reflect the ineffectiveness of digital delivery rather than the ineffectiveness of the intervention. In this case, an RCT testing in-person delivery would be indicated.

The 6MWT is known to be influenced by motivation. The use of the Borg Dyspnea Inventory is used as a control on this, as it indexes amount of effort, and every precaution has been taken by the researchers to standardize the administration of the test. Nonetheless, in the Selection stage, subjects may be more highly motivated in the post-test situation, and this could skew results. As mentioned above, the use of a control group in the RCT stage will provide a check on these results.

In the RCT stage, compliance is expected to be an issue. We plan to be in contact by email, phone, and digital questionnaire with all subjects on a weekly basis. We will follow up quickly any lapses in communication or reporting of difficulties, so as to minimize this issue. Such difficulties arising in this stage will also provide further information for future refinement of the delivery method and the selection of exercises.

## Discussion

We believe that the ANS may be a link between the various co-morbidities of COPD.

We speculate that COPD-related pulmonary and other co-morbid conditions appearing in FA exposed to SHCS may be part of a syndrome of interacting conditions related to disturbed autonomic function. The Screening stage of this study will provide data to test this speculation.

In addition to our primary outcome measures, we are gathering a wide range of data, including hormonal biomarkers, affective, and autonomic measures. This may allow for the formulation of hypotheses for future testing concerning the mechanisms of action of MM on pulmonary dysfunction and other health conditions. In preliminary data, we are seeing patterns of subclinical morbidities that may provide an improved picture of the health care needs of this unique group of workers. It, however, remains to be seen whether these patterns are simply age related or unique to this group and their exposure to SHCS.

Since MM has been shown to have beneficial effects on many of the co-morbid conditions of COPD, possibly by way of its regulating effect on autonomic functioning, this suggests that a single approach (MM) might target not only COPD-related respiratory symptoms but also many other COPD-related conditions. Future studies could determine whether MM could slow the progression of pre-COPD conditions to clinical COPD.

Previous trials of the effects of MM have relied on a preselected set of exercises, in some cases chosen for their traditional relevance to the condition being treated (57) but in most cases a traditional general set (30, 32–36). Our study is the first to involve a test period in which a wide range of MM exercises is evaluated for a specific population. We have already observed that participants have trouble setting aside time for regular practice. Our approach to MM includes a number of practices that can be integrated with the activities of daily life (rather than having to be practiced at a certain time), and we have found that this form of practice is more acceptable to this group of FA.

We experienced an unexpected level of dropout during the Selection stage of the study. Given that the average age of participants is 69, this should have been anticipated. We have found that the provision of exercises that can be integrated into daily life, such as simple standing, sitting, walking, and breathing practices, increases compliance and appears to reduce dropout. We believe that the emphasis on this kind of practice can make Asian practices more accessible and appealing to Westerners with their busy lifestyles.

Our study explores the possibility of administering an MM intervention by digital means. To our knowledge, no other study of MM has tested this possibility. Information gained from this aspect of the study may provide information about the most effective ways of conveying MM training digitally, as well as validating the effectiveness of MM for COPD-related pulmonary dysfunction. Should our principal hypothesis be supported, it would not only open the possibility of a safe, cost-effective intervention for those with pulmonary dysfunction, but also support the further exploration of digitally delivered MM for a wide range of conditions, especially those with a significant autonomic component.

